### 10.6 Data Safety Monitoring Committee

The DSMC will be independent and consist of a statistician and two content experts uninvolved in the trial. The DSMC will meet every six months after study initiation to review toxicity outcomes. If any grade 3-5 toxicity is reported, the DSMC will review cases notes to determine if such toxicity is related to treatment. If the DSMC deems that toxicity rates are excessive (>25% grade 3 toxicity or >5% grade 4/5 toxicity) then the DSMC can, at its discretion, recommend cessation of the trial or dose adjustment. The DSMC may consider removing a dose level if the rate of clinically significant change in ECS (defined as 2 point change from baseline) occurs in <10% of patients in the control arm. If the DSMC decides that review of toxicity data by email (rather than in-person DSMC meetings) is sufficient because of low toxicity rates, this will be acceptable.

Interim analysis: the DSMC will conduct one interim analysis once 30 patients are accrued. The rationale for this analysis is to ensure that trial accrual is proceeding in a timely manner and to terminate the trial if early stopping rules are met. In this analysis, the DSMC will be blinded to the identity of each treatment arm, but ECS data and OS will be presented for each arm. The DSMC will recommend stopping the trial if there is a statistically significant difference with  $p < 0.001$  using Student's t-test (Haybrittle-Peto stopping rule) in ECS or OS between the two arms. Furthermore, if the measured differences in esophageal QOL are substantially different than estimated in the sample size calculation, the DSMC can recommend increasing or decreasing the target accrual in order to maintain statistical power.

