### 9.1 Measurement of Outcomes

#### 9.1.1. Time-to-event outcomes

Overall survival will be measured as time from randomization to death from any cause.

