### 10.4 Sample size calculation

Regarding the primary endpoint, a change in ECS score of 2 to 3 points is considered clinically relevant. We will assume there will be a moderately large effect size (0.65), and a non-responder rate of 15% (5). Using a two-sided, independent-sample t-test with an alpha level of 0.05 and power of 80%, to detect a clinically relevant ECS change in the experimental arm, 90 patients will be required (45 in each arm).

We anticipate that 1-2 patients could be accrued each month at each participating institution, yielding approximately 30 patients per year. The study thus projects accrual over 4 years with 12 months of additional follow-up. Accrual for the sample size calculated is feasible in the Canadian multi-institutional context.

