#### ***Primary Endpoint***

Esophageal quality of life will be calculated by tabulating FACT-E scores at 2 weeks, with differences between groups tested using the Student's t-test.

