#### ***Secondary Endpoints***

Additional QoL endpoints will be analyzed by compiling relevant EQ-5D values, FACT subscale and trial outcome index (TOI) scores. Treatment arm differences will be analyzed using linear mixed-effects models. Survival will be calculated Kaplan-Meier method with differences compared using the stratified log-rank test. Differences in rates of grade 2 or higher toxicity between groups will be tested using the Fisher's Exact test. Differences in the number of cycles of further systemic therapy will be tested using the student's t-test. EQ-5D measurements will be converted into utilities to inform cost-effectiveness/utility analyses. Finally dosimetric comparison of GTV, PTV, as well as standard pulmonary and esophageal metrics will be compared using the student's t-test.

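### The interim stopping rule applies Student's t-test to overall survival, a censored endpoint that the protocol itself analyses with the stratified log-rank test

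*Protocol*

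**What the plan says.** Section 10.6 plans a single look: "the DSMC will conduct one interim analysis once 30 patients are accrued". At that look "ECS data and OS will be presented for each arm", with the identity of the arms masked. The DSMC is to recommend stopping at p < 0.001 "using Student's t-test (Haybrittle-Peto stopping rule) in ECS or OS between the two arms". One test is named and it governs both endpoints; no other interim test for survival appears in the protocol.

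Elsewhere the two endpoints are handled differently:

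- **ECS.** Section 10.5, Primary Endpoint, compares the arms by "tabulating FACT-E scores at 2 weeks, with differences between groups tested using the Student's t-test".
- **OS.** Section 9.1.1, under a heading for time-to-event outcomes, states: "Overall survival will be measured as time from randomization to death from any cause". Section 10.5, Secondary Endpoints, states: "Survival will be calculated Kaplan-Meier method with differences compared using the stratified log-rank test".

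**The concern.** The t-test in the stopping rule matches the planned analysis of ECS but not that of OS. The likely cause is a phrase meant for ECS that was stretched to cover both endpoints. The look comes while patients are still entering, so many survival times will be incomplete, and a t-test cannot use an incomplete time as such.

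This is not a detail left to a later analysis plan, because the protocol names the test. A DSMC statistician who sensibly used the log-rank test would depart from the written rule. One who followed the rule would have to choose, without guidance, how to treat patients still alive.

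At stake is the only formal between-arm rule on survival in the protocol. The experimental arm accepts underdosage of part of the target volume (section 6.2), so a survival comparison that works is worth having.

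**Working it through.** **1. The plan's own figure.** Section 10.4 gives an effect size of 0.65, two-sided alpha 0.05, power 80% and 15% non-response. Per arm, n = 2 × (1.960 + 0.842)² / 0.65² = 37.2, rounded up to 38. Then 38 / 0.85 = 44.7, rounded up to 45, so 90 in total. The stated 90 reproduces. It rests on ECS alone and is untouched by the choice of survival test.

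**2. Follow-up at the look.** Section 10.4 expects about 30 patients a year, so the 30th enters at about month 12. With even entry, follow-up runs from 0 to about 12 months.

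**3. Share of survival times censored.** The protocol gives no median survival, so medians of 4, 6 and 9 months are assumed, with exponential survival and equal arms. With λ = ln 2 / median and A = 12 months, the censored share is (1 − e^(−λA)) / (λA).

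| Assumed median | λA | Censored share | Expected deaths of 30 |
|---|---|---|---|
| 4 months | 2.079 | 0.875 / 2.079 = 42% | 17.4 |
| 6 months | 1.386 | 0.750 / 1.386 = 54% | 13.8 |
| 9 months | 0.924 | 0.603 / 0.924 = 65% | 10.4 |

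Section 10.4 also projects accrual over 4 years. At 90 / 4 = 22.5 patients a year the look would fall at month 16, and the same formula gives 0.9375 / 2.773 = 34% censored (median 4) to 0.708 / 1.232 = 57% (median 9). Censoring is substantial either way.

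**4. What a t-test can do with these data.** There are two options. It can take time on study for everyone, which treats a patient who entered last month and is alive as if survival were one month. Or it can take only those who died, which discards the living and compares early deaths with early deaths. Neither quantity is survival.

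**5. False stopping.** Simulating the design with no true difference (15 per arm, uniform entry over 12 months, cut at month 12), the t-test on observed times rejects about 4.7 to 5.3% of the time at the nominal 5% level. With equal censoring by arm there is no inflation.

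**6. Sensitivity.** Same design, several thousand simulated trials per scenario, medians of 4 to 9 months in the better arm, and the two dose strata about equally filled. Chance of crossing p < 0.001:

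| True hazard ratio | Stratified log-rank | t-test on observed times |
|---|---|---|
| 2 | about 1–3% | about 0.3–1% |
| 3 | about 7–13% | about 3–6% |
| 4 | about 20–33% | about 8–14% |

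A t-test on deaths only does worse: at a hazard ratio of 4 and medians of 6 to 9 months it crosses in about 1.4 to 3.5% of trials.

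**The case against.** The best case for leaving this alone is that it changes little. OS is secondary, its final analysis in section 10.5 is already right, and the slip touches one look at 30 patients. At a hazard ratio of 2, naming the correct test raises the chance of stopping by only one or two percentage points, and about 97% or more of such trials would still continue. That stands, and it limits how much weight the point can carry.

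A reader might also infer four stronger things that the documents do not support:

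- **That the t-test makes the rule blind to harm.** At moderate effects, most of the insensitivity comes from p < 0.001 with 30 patients. The gap between the tests becomes large only at hazard ratios of 3 or 4, which are extreme for two arms given the same prescribed dose.
- **That the t-test would cause false stopping.** With equal censoring by arm, step 5 shows that it does not.
- **That most survival times are censored.** This depends on the assumed median. At 4 months and equal arms the share is about 42%.
- **That nothing else in the protocol responds to deaths.** Section 10.6 lets the DSMC recommend cessation if grade 4/5 toxicity exceeds 5%, and grade 5 is death. But that trigger is discretionary and tied to treatment-related toxicity, and section 7.4 keeps disease progression out of SAE reporting. It does not compare survival between the arms.

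None of this defends the named test. No other section supplies a different interim test for OS.

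**Conclusion.** The point holds as an error in the written rule. Section 10.6 names a test that cannot compare censored survival times and that differs from the protocol's own test for the same endpoint. The fault is a wrong quantity and lost sensitivity: in the scenarios examined, the t-test on observed times crosses the boundary roughly half as often as the stratified log-rank test, or less. In absolute terms the loss is small at a hazard ratio of 2 and reaches about 12 to 19 percentage points at 4 (20 − 8 and 33 − 14).

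These sizes rest on assumed exponential survival, assumed medians and hazard ratios, and even entry over 12 months; the protocol gives no median or hazard ratio. The mismatch of tests needs none of these assumptions. The sample size, the ECS rule and the final OS analysis are unaffected.

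**What to change.** In section 10.6, name one test per endpoint. Suggested wording: *The DSMC will recommend stopping if p < 0.001 by Student's t-test for ECS at 2 weeks, or p < 0.001 by the log-rank test stratified by prescribed dose for OS.* Both tests then match section 10.5.

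The cost is one clause in a protocol amendment, with no change to the sample size, the data collected or the timing of the look. Make it before the interim data are seen, since changing a stopping test afterwards would compromise the rule. It would also help to tell the DSMC that the formal survival test has low power at 30 patients, so that a result short of the boundary is not read as reassurance.

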### 10.3 Stratification

The sample size calculated allows for one stratification factor at randomization, which will be the prescribed dose (20 Gy/5# vs. 30 Gy/10#).

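### The interim stopping rule names Student's t-test for overall survival, a test that cannot properly use patients still alive and that contradicts the stratified log-rank test in Section 10.5

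*Protocol*

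**What the plan says.** Section 10.6 states that "the DSMC will conduct one interim analysis once 30 patients are accrued". The DSMC does not know which arm is which, but it sees ECS and OS for each. The rule then reads: "The DSMC will recommend stopping the trial if there is a statistically significant difference" at p<0.001 "using Student's t-test (Haybrittle-Peto stopping rule) in ECS or OS between the two arms". One test is named, and grammatically it governs both endpoints. The rule is firm about what the DSMC will recommend, whereas the toxicity rule in the same section leaves the matter to the DSMC's discretion.

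Elsewhere the protocol treats OS as a time-to-event outcome. Section 9.1.1 says: "Overall survival will be measured as time from randomization to death from any cause". Section 10.5 (Secondary Endpoints) uses Kaplan-Meier estimates with "differences compared using the stratified log-rank test". Section 10.3 gives "one stratification factor at randomization, which will be the prescribed dose". For the primary endpoint, Section 10.5 uses Student's t-test on the 2-week score, so the interim test for ECS agrees with the final one.

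No other section names a different interim test for OS or says how living patients would enter a t-test.

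**The concern.** A t-test compares means of fully observed values. The look is triggered by the 30th entry, not by deaths or completed follow-up, so the newest patients have almost no follow-up and many of the 30 will be alive. There are two ways to force OS into a t-test:

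- **Follow-up time for everyone.** A patient alive one week after entry then counts as a shorter survival than one who died at six months.
- **Deaths only.** Everyone still alive is dropped.

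Neither uses the information in censored times as the log-rank test does, and the protocol does not choose between them. At stake is whether one of the two efficacy criteria for stopping can be applied as written, and whether it matches the method by which the same endpoint is finally judged.

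**Working it through.** **1. The plan's own figure.** Section 10.4 gives an effect size of 0.65, two-sided alpha 0.05, power 80% and 15% non-response. Per arm, n = 2(1.960 + 0.842)²/0.65² = 37.2, rounded up to 38. Then 38/0.85 = 44.7, so 45 per arm and 90 in total, as stated. This calculation concerns ECS only, so changing the interim test for OS does not touch it.

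**2. The tests side by side.**

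| Endpoint | Interim test (10.6) | Final test (10.5) |
|---|---|---|
| ECS | Student's t-test | Student's t-test |
| OS | Student's t-test | Stratified log-rank |

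Only the OS row conflicts.

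**3. How many patients are censored at the look.** Section 10.4 gives about 30 patients per year, and also 90 patients over 4 years (22.5 per year). The 30th patient therefore enters at month A = 12 or A = 16. The protocol states no survival rates, so I assume exponential survival with a median of 6, 9 or 12 months, uniform entry and no difference between arms. With rate λ = ln 2/median, expected deaths at the look are

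30 × [1 − (1 − exp(−λA))/(λA)].

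For example, with A = 12 and median 6, λA = 1.386 and deaths = 30 × (1 − 0.750/1.386) = 13.8.

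| Median OS (months) | A = 12: deaths (censored) | A = 16: deaths (censored) |
|---|---|---|
| 6 | 13.8 (54%) | 16.3 (46%) |
| 9 | 10.4 (65%) | 12.8 (57%) |
| 12 | 8.4 (72%) | 10.4 (65%) |

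These are counts under no difference. If one arm has twice the hazard of the other, whose median is 6 to 12 months, about 11 to 19 deaths are expected. With A = 12 and medians 12 and 6: 15 × 0.279 + 15 × 0.459 = 11.1. With A = 16 and medians 6 and 3: 15 × 0.544 + 15 × 0.736 = 19.2.

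**4. Chance of crossing p<0.001.** Simulation with 10,000 runs per setting, both accrual rates, all three medians, two equal dose strata and permuted blocks of 4 (stratum split and block size are assumed), and censoring only by the date of the look. Ranges are over the six settings.

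| Test for OS | HR 1 | HR 1.5 | HR 2 |
|---|---|---|---|
| Stratified log-rank | 0.05-0.15% | 0.28-0.53% | 0.8-2.7% |
| t-test on follow-up time | 0-0.03% | 0.02-0.11% | 0.1-0.5% |
| t-test among the dead | 0.08-0.15% | 0.15-0.23% | 0.2-0.5% |

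The Monte Carlo standard error in the HR 1 column is about 0.03 percentage points.

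**5. Sensitivity.** A separate simulation at A = 12, with 20,000 runs per setting, no blocking and an unstratified log-rank test, put the benefit in the other direction. At HR 0.25 and medians 6, 9 and 12, crossing was 5.7%, 2.0% and 0.8% for log-rank, 1.5%, 0.8% and 0.4% for the t-test on follow-up time, and 0.3%, 0.1% and 0.1% for the t-test among the dead. Under no difference every test crossed in about 0.1-0.2%. The ordering of the tests at a true difference is the same.

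**The case against.** The best defence is that this is loose drafting: a phrase written for ECS with OS appended, in a protocol that names the right test one section earlier. A single look at 0.001 on a secondary endpoint will hardly ever trigger, whichever test is used, and the outcome is a recommendation. All of that is fair, and it limits the weight of the point. It does not remove it, because the sentence as it stands fixes the test rather than leaving it to a later document.

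Three stronger readings are tempting, and the documents do not support them.

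- **That the t-test is biased or raises the risk of false stopping.** Randomization in permuted blocks (Section 10.1) balances entry times between arms. The follow-up-time version is therefore inefficient and conservative rather than biased: it crosses in at most 0.03% of null trials with blocks of 4, against a nominal 0.1%.
- **That the DSMC would have to choose a method after seeing the data.** A charter or analysis plan could settle the handling of living patients before the look. The DSMC includes a statistician and is blinded to arm identity.
- **That the two versions of the t-test would send the DSMC in opposite directions.** Their signs differ in roughly 20-35% of simulated trials at HR 2, but the rule acts only at p<0.001. Opposite signs with either version below that level occurred in at most about 0.03% of trials.

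**Conclusion.** The point holds as a wrong and internally inconsistent test in a firm stopping rule. Section 10.6 applies to OS a test that cannot properly use the patients still alive, about 46-72% of the 30 under no difference, and Section 10.5 analyses the same endpoint by another method.

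The practical effect is small. At HR 2 the correct test crosses in about 1-3% of trials and either version of the t-test in under 1%, so little chance of stopping is lost, and false stopping is not inflated. These sizes rest on assumed medians of 6 to 12 months, exponential survival, uniform entry and illustrative hazard ratios. The contradiction between the two sections rests on none of them.

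A reader might also infer that the DSMC is kept from seeing deaths at its six-monthly meetings, since the text says "The DSMC will meet every six months after study initiation to review toxicity outcomes". That does not follow. The section does not exclude deaths, grade 5 events count as toxicity, and report content is commonly set in a charter.

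The correction should be made because it is cheap and concerns a stopping rule, not because the trial's conclusions are at risk.

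**What to change.** Reword the rule in Section 10.6 along these lines: *Stopping will be recommended when the two arms differ at p<0.001 either in ECS, by Student's t-test, or in OS, by the stratified log-rank test of Section 10.5 with prescribed dose as the stratum.* Section 10.5 says only that the log-rank test is stratified. The factor comes from Section 10.3, so it is worth naming.

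Keep the 0.001 threshold, the t-test for ECS, the timing of the look and the sample size of 90. The cost is one phrase, with no new data or patients. Under no difference the stratified log-rank test crosses in 0.05-0.15% of simulated trials, in line with the nominal 0.1%, so no alpha adjustment is needed.

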## **10.0 STATISTICS AND SAMPLE SIZE CALCULATIONS**

### 10.1 Randomization

Patients will be randomized in a 1:1 ratio between Arm 1 and Arm 2. The sample size allows for one stratification factor at randomization: the prescribed RT dose. Randomization will occur in permuted blocks, with the block size known only by the statistician.

A randomized design is indicated for the following reasons:

1. Historically, esophagitis following RT for lung cancer has been measured mostly

through CTCAE, and such data may not provide an appropriate control due to various sources of biases from patient selection, technical RT factors and other comparisons. Thus randomization will provide a more appropriate control group to serve for the experimental arm, particularly when using the FACT-G and cancer subscales.

2. The sample size calculated allows for adequate power to detect a clinically meaningful change in esophageal quality of life

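### Accrual may be raised or lowered on the observed between-arm ECS difference at 30 patients, without rule or limits; if the option is used, the ordinary 0.05 t-test is not guaranteed to keep a 5% type I error

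*Protocol*

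**What the plan says.** Protocol section 10.6 plans one interim analysis once 30 patients are accrued. Arm identities are masked, but ECS and OS are shown for each arm. The DSMC is to recommend stopping if ECS or OS differs at p<0.001. The next sentence, the last of the section, adds a second use of the same data: "if the measured differences in esophageal QOL are substantially different than estimated in the sample size calculation", then "the DSMC can recommend increasing or decreasing the target accrual in order to maintain statistical power". The trigger is the measured difference itself, not its variability or the rate of missing questionnaires. The section does not say what counts as substantial, how the new size is computed, or how far it may move.

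The design value is in section 10.4: "We will assume there will be a moderately large effect size (0.65), and a non-responder rate of 15" per cent. The test there is given by "Using a two-sided, independent-sample t-test with an alpha level of 0.05 and power of 80" per cent, and the result is 90 patients, 45 per arm. The same section says that "a change in ECS score of 2 to 3 points is considered clinically relevant", but it names neither a single target difference in points nor an SD.

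Section 10.5 (Primary Endpoint) gives the final analysis as 2-week FACT-E scores, "with differences between groups tested using the Student's t-test". The protocol mentions no weighting or adjusted critical value for use after accrual has been changed.

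**The concern.** When the final sample size depends on the interim effect, the weight that the first 30 patients carry in the final statistic depends on their own result. After a large early difference, fewer new patients are added and the early result keeps a high weight. After a small one, many are added and the early result is diluted. Under no true effect, both moves raise the chance of a nominally significant final test, which an ordinary t-test ignores. At stake is the stated two-sided 5% level for the primary endpoint of a phase III trial.

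The downward option also interacts with the stopping rule in the preceding sentence. A p<0.001 boundary is meant to keep an early, noisy result from deciding the trial. A cut in accrual after a large early difference moves the 0.05 test closer to that same early result.

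**Working it through.** **1. The planned size reproduces.** Per arm, n = 2(1.960 + 0.842)²/0.65² = 15.70/0.4225 = 37.2, rounded up to 38 evaluable. Allowing for 15% non-response, 38/0.85 = 44.7, rounded up to 45 per arm, or 90 in total. An exact t calculation gives 39 evaluable, hence 46 per arm and 92 in total. The planned size is not in dispute.

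**2. What the DSMC would see.** Thirty patients are 15 per arm, and 15 × 0.85 = 12.75, so about 13 evaluable per arm. The standard error of the standardised difference is √(2/13) = 0.39. If the true effect is 0.65, the observed one falls within 0.65 ± 1.96 × 0.39 in 95% of trials, that is, from about −0.1 to 1.4. It will often look different from plan by chance.

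**3. How the error arises.** Let n₁ = 13 be the evaluable number per arm at the look, N the final number per arm and z₁ the interim statistic. In the z approximation, the final test rejects in the direction of the interim result with conditional probability, under no effect, of 1 − Φ[(1.96√N − z₁√n₁)/√(N − n₁)]. The other tail has +z₁ in place of −z₁.

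- Large early difference, observed effect 0.85: z₁ = 0.85/0.392 = 2.17, p = 0.03, so the p<0.001 rule says continue. With N = 38 the conditional chance of a false positive is 20%. Resizing for 80% power at the observed effect gives 15.70/0.85² = 21.7, so N = 22, and the chance becomes 32%.
- Small early difference, observed effect 0.10: z₁ = 0.25. With N = 38 the chance, both tails, is 1.7%. If N is raised to an assumed cap of 76 it becomes 3.2%.

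**4. Overall type I error by simulation.** All runs are under no effect with the p<0.001 stop kept. N is reset for 80% power at the observed effect, within limits. The limits and the trigger are assumptions, because the protocol gives none. The trigger used is resizing only if the observed effect is at least 0.325 away from 0.65, half the planned effect.

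| Evaluable N per arm allowed | Type I error |
|---|---|
| Fixed at 38 | 5.0% |
| 34 to 45, with trigger | 5.3% |
| 34 to 45 | 5.4% |
| 30 to 57 | 5.9% |
| 25 to 76, with trigger | 6.1% |
| 25 to 76 | 6.4% |
| 20 to 76 | 6.8% |
| 14 to 152 | 7.6% |
| Increase only, 38 to 76 | 5.8% |
| Decrease only, 25 to 38 | 5.7% |

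A separate set of runs used t-tests with 15 of 45 per arm at the look. It gave 5.5% to 6.1% for increase only (caps of 1.5 to 3 times plan) and 5.7% to 6.7% for decrease only. With both directions allowed, a floor just above interim size and a cap of 3 times plan, it gave 7.7%. If N were chosen at each interim value to do the most harm, between the interim size and twice the plan, the bound is about 10%.

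**5. Source of the inflation.** The same resizing rules were run with stage weights fixed in advance: final z = √(30/90)·z₁ + √(60/90)·z₂, where z₂ uses only patients after the look. Type I error was 5.0% to 5.1% in every scenario. The inflation therefore comes from the effect-driven N combined with the ordinary test. The p<0.001 look itself adds only about 0.05 percentage points.

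**The case against.** Several points on the other side stand. The option is discretionary and applies only after a substantial departure, so nothing is inflated if it is never used. The size of the inflation rests on limits that the protocol does not contain; with tight limits it is about 0.3 percentage points. A statistical analysis plan that is not shown could specify an adjusted final test. Increases confined to promising interim results (conditional power of at least 50%) would not inflate the error.

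These points limit the finding but do not remove it. Section 10.6 does not confine the option to promising results, sets no cap or floor, and allows decreases as well. The effect-driven trigger is fixed in this document, whatever another document may add.

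Two defences do not work. Masked labels give no protection: per-arm data show the absolute difference, the test is two-sided, and every simulation above resized on the absolute difference alone. The p<0.001 rule covers stopping at the look, not a change in N.

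A reader might infer that the 5% level is simply lost, or that the p<0.001 rule is nullified. The document supports neither. The level fails only if the option is used under an unadjusted test. A lower target approaches a stop only if it is set near the interim size, and the p<0.001 rule still governs stopping at the look itself.

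**Conclusion.** The concern holds in conditional form. As written, section 10.6 permits an effect-driven change of sample size without rule or limits, and the protocol pairs it only with an ordinary two-sided 0.05 t-test. If the option is used, the stated 5% is not guaranteed. Under the assumed limits, type I error is about 5.3% to 7.7%, against 5.0% with N fixed. This is a range under assumptions, not one figure, and the protocol gives no basis for narrowing it. The imprecision of the interim estimate is a separate, lesser point. It concerns efficiency: if 0.65 is true, a chance-high estimate would prompt a cut that loses power, contrary to the stated purpose of the rule.

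**What to change.** Replace the last sentence of section 10.6 with wording such as: *Target accrual may be reassessed once, using only the arm-blind pooled SD of the 2-week ECS and the pooled non-response rate, with the target difference held at the value in section 10.4. Accrual will not be changed on the observed between-arm difference.*

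This cannot be applied until section 10.4 states the single raw ECS difference, within the 2 to 3 points, and the SD that together give 0.65. The implied SD runs from 2/0.65 = 3.1 to 3/0.65 = 4.6. For a given SD, the required size differs by (3/2)² = 2.25-fold between the two ends, so the choice matters.

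If effect-based resizing is to stay, pre-specify its trigger, formula, cap and floor. Fix the stage weights at 30/90 and 60/90, and make the final primary test the inverse-normal combination test shown in step 5, which restores about 5.0%.

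The cost is a short amendment to sections 10.4 and 10.6, and to 10.5 if the combination test is chosen. Under the first option the DSMC gives up resizing on the early effect. Under the second the final test becomes slightly more complex.
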